## The role of the therapist

Each participant is assigned a designated therapist who provides guidance and support in both trial arms, answers questions, and gives feedback on digital worksheets. To ensure consistent access, therapists log into the platform on three pre-specified weekdays (Monday, Wednesday, and Friday) for all participants to review progress and to address messages even if no new message has been posted. Guidance is proactive: each participant receives at least one substantive feedback message per week irrespective of participant-initiated contact, and therapists reply within 48 h on business days to any incoming message. Completion of a module and submission of exposure worksheets trigger targeted feedback within 48 business hours. This login cadence and response-time standard are identical across arms and are communicated to participants at onboarding. Brief telephone check-ins may be conducted when clinically indicated; such contacts are considered protocol deviations and are logged in the eCRF.

Participants complete the PCL-5 weekly within the platform, accompanied by an open-ended question about any adverse events including perceived intensity and duration. When PCL-5 scores or AE reports indicate exacerbation, the default response is delivered via secure platform messaging: the therapist validates and normalizes transient symptom increases, screens for risk, reviews adherence and possible safety behaviors, and titrates exposure intensity (e.g., temporarily shortening imaginal exposure assignments or stepping down in vivo tasks, then re-escalating as tolerated) while maintaining fidelity to PE. If elevated distress persists or risk is suspected, the therapist may conduct a brief telephone check-in to complete a focused risk assessment and agree on next steps; such calls are treated as protocol deviations and logged in the eCRF. All routine assessments and contacts are remote, and no face-to-face visits are planned. Acute risk is managed per the study safety protocol, including immediate clinical escalation and referral to regular care services (e.g., emergency psychiatric services, local outpatient psychiatry, or the emergency department), with activation of emergency services when indicated; all actions are documented in the eCRF.

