### Criteria for discontinuing or modifying allocated interventions {11b}

Participants may withdraw their consent to participate in the treatment and the trial at any timepoint. Suicidal ideation triggers a structured suicide-risk assessment (e.g., C-SSRS plus focused interview on intent, plan, means, and protective factors) and, if indicated, referral. All safety assessments are conducted remotely (telephone or secure video), no face-to-face visits are planned. The intervention may be temporarily titrated or discontinued for (a) acute suicide risk requiring urgent care or (b) emergent medical/psychiatric conditions that render participation unsafe. Acute risk is managed per the study safety protocol with immediate escalation and referral to regular care (e.g., emergency psychiatric services, local outpatient psychiatry, emergency department). Participants who discontinue the intervention are invited to continue all scheduled outcome assessments when clinically appropriate.

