### Strategies to improve adherence to interventions {11c}

The platform sends automated SMS reminders at each scheduled weekly monitoring point and an SMS notification whenever a therapist posts a message. If a participant has not logged in for 3 consecutive days, the therapist sends a personalized SMS via the platform to prompt engagement. If inactivity reaches 5 consecutive days, the therapist attempts telephone contact; if phone contact cannot be established, a letter is mailed within the same week. Automated digital reminders continue, and the therapist re-attempts contact weekly thereafter unless the participant withdraws consent. (This escalation schedule is identical across trial arms.)

Participants who discontinue treatment are retained in follow-up whenever possible and invited to complete all scheduled outcome assessments; this approach minimizes attrition bias and supports valid intention-to-treat analyses.

The therapist delivering the treatments in the trial will comprise resident psychologists (a 1-year post-degree licensure period following a 5-year MSc in Psychology). All clinicians are based at a specialized PTSD unit and deliver treatment in both trial arms. All therapists will receive training in and a written treatment manual for both treatment arms. Supervision by certified supervisors and trainers in prolonged exposure and/or CBT will be offered weekly.

Blinded assessors will undergo a minimum of a full-day training in the CAPS-5 prior to conducting clinician-rated assessment with CAPS-5 and practice by rating videos of fictious PTSD case examples. Assessors who deviate more than 10% of the CAPS-5 total score agreed upon by one of the authors (MB) and score more than one point differently on a maximum of four single items will need to retake the training. The assessors are offered weekly supervision.

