### Methods in analysis to handle protocol nonadherence and any statistical methods to handle missing data {20c}

All available data will be used in the models. All protocol deviations will be reported.

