### Adverse event reporting and harms {22}

Participants can report the occurrence of undesirable treatment effects at any point through the study period by alerting the designated therapist on the digital platform or assessor or contacting the study personnel. Weekly measures to capture any unwanted adverse events will be administered, including questions about intensity, duration, and characteristics of the adverse event.

All potential undesirable treatment effects will be categorized by the investigator into three levels: mild, moderate, or severe. An event will be deemed serious if it poses a life-threatening risk, leads to death, causes persistent or significant disability/incapacity, necessitates hospitalization or its prolongation, or is determined to be medically significant by the principal investigator. The Negative Effects Questionnaire (NEQ) will be utilized posttreatment and during follow-ups to systematically gather data on potential adverse effects.

Therapists will be needed to promptly inform the principal investigator if they have concerns that a participant has caused, or is at risk of causing, significant harm to themselves or others or discloses any suicidal ideation. In such cases, a suicide risk assessment will be conducted over the phone to ensure appropriate and immediate support.

All participants in the study will receive active treatments with previous support by clinicians who specialize in the treatment of PTSD. Previous studies that have investigated intensive prolonged exposure have not detected any serious adverse events. The additional risks associated with participating in digital HOPE are hence considered to be small. All participants will be closely monitored during the study, and additional treatment will be provided in case of an unlikely severe deterioration.

Excluded participants will be informed where to seek help in the regular health care system. After the 1-month follow-up, participants will be offered the treatment they were not originally allocated to.

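### A telephone risk assessment is optional and a protocol deviation in one section but prescribed in others, so safety calls made as directed would count as reported deviations

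*Protocol article*

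**What the plan says.** Five places in the protocol article bear on this.

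- **The role of the therapist**, first paragraph, sets a general status for telephone contact: "Brief telephone check-ins may be conducted when clinically indicated; such contacts are considered protocol deviations and are logged in the eCRF". The second paragraph applies it to risk: "If elevated distress persists or risk is suspected, the therapist may conduct a brief telephone check-in to complete a focused risk assessment", followed by "such calls are treated as protocol deviations and logged in the eCRF".
- **Criteria for discontinuing or modifying allocated interventions {11b}**: "Suicidal ideation triggers a structured suicide-risk assessment". On mode it adds: "All safety assessments are conducted remotely (telephone or secure video), no face-to-face visits are planned".
- **Adverse event reporting and harms {22}** has therapists inform the principal investigator promptly when they fear serious harm to self or others, or when suicidal ideation is disclosed. It continues: "In such cases, a suicide risk assessment will be conducted over the phone to ensure appropriate and immediate support".
- **Section {20c}** states "All protocol deviations will be reported", with no exemption for safety contact.
- **Strategies to improve adherence to interventions {11c}** schedules a different kind of call: "If inactivity reaches 5 consecutive days, the therapist attempts telephone contact".

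**The concern.** A step that a protocol prescribes cannot also be a departure from it. Here a remote risk assessment is discretionary and a deviation in one section, and directed without any such label in two others.

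Two things are at stake. The first is the meaning of the deviation report. If risk calls made as directed are logged as deviations, the report mixes compliance with departure. A difference between arms could then reflect safety procedures being followed rather than poorer conduct. The protocol relies on matched therapist contact between arms (section {6b}), so readers may well look at deviations involving telephone contact.

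The second is consistent conduct. Therapists read *may* in one section and *will* in another on contact about suicide risk.

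**Working it through.** No arithmetic applies: the article gives no call rate and no deviation count to reproduce. The check is a comparison of the sections.

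| Section | Trigger | Caller | Mode | Optional or prescribed | Called a deviation? |
|---|---|---|---|---|---|
| The role of the therapist | Persisting distress or suspected risk | Therapist | Telephone | Optional (*may*) | Yes |
| {11b} | Suicidal ideation | Not named | Telephone or secure video | Prescribed (*triggers*) | No |
| {22} | Fear of serious harm, or any disclosed suicidal ideation | Not named; therapist informs the principal investigator | Telephone | Prescribed (*will*) | No |
| {11c} | 5 days of inactivity | Therapist | Telephone | Prescribed | No; not a risk call |

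1. **Do the triggers overlap?** Yes. Disclosed suicidal ideation, the trigger in {11b} and {22}, is also a case of suspected risk under The role of the therapist.

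2. **Is the purpose shared?** Yes. The role of the therapist gives a focused risk assessment as the reason for its call. Sections {11b} and {22} both describe a suicide-risk assessment done remotely.

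3. **Does the status differ?** Yes, in two respects: optional against prescribed, and deviation against no such label.

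4. **Worked case.** A participant discloses suicidal ideation in a platform message. Under {22} the principal investigator is informed and a telephone assessment follows. If the therapist makes that call, it is also a telephone risk assessment on suspected risk, which The role of the therapist classes as a deviation. Under {20c} it is then reported as one.

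5. **Where the overlap stops.** An assessment done by video under {11b} is not a telephone call, so the deviation label does not reach it. If someone other than the therapist makes the {22} call, the article does not say whether the label applies. The {11c} inactivity call has its own trigger, and no text labels it a deviation.

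6. **Does it reach the primary analysis?** No. Section {20a} applies intention-to-treat, and nothing in the article excludes participants for deviations. The CAPS-5 comparison, the two-sided alpha of 0.05 and the planned 286 participants do not depend on how a call is classified.

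**The case against.** The strongest reply is that these are different acts on a ladder: platform messages by default, then a brief check-in, then acute risk handled under a separate safety protocol that is not shown. The deviation label would belong only to the middle step. On this view {11b} describes a structured instrument, {22} follows notification of the principal investigator, and logging any contact outside the digital format is a transparent choice in a design built on matched contact.

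Part of this stands. Logging such calls is reasonable, and the acute-risk step is not itself labelled a deviation. But the article does not draw the line the reply needs. It puts the label on a call whose stated purpose is risk assessment and whose stated trigger includes suspected risk. Nor is this a detail left to a fuller document, since the article itself makes both statements.

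Several stronger readings are tempting and are not supported:

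- *That telephone is mandatory in both other sections.* Only {22} fixes the telephone; {11b} also allows video.
- *That therapists are forbidden or deterred from calling.* The call is expressly permitted, {22} names no caller, and any deterrent effect of the label is conjecture.
- *That inactivity calls are deviations too.* No text says so.
- *That true differences in contact would be hidden.* The Treatment variables section separately collects therapist time per participant, including off-platform calls.
- *That the number of participants affected can be put at some share of the 286.* The article gives no rate on which to base one.

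**Conclusion.** The contradiction stands, in a limited form. The role of the therapist makes a telephone risk assessment optional and a deviation. Section {22} prescribes one by telephone, and {11b} prescribes one by telephone or video, for overlapping triggers and the same purpose. Followed literally, the text places risk calls that the protocol directs among its reported deviations, and it gives conflicting instructions on whether the assessment is optional.

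The conclusion rests on reading disclosed suicidal ideation as a form of suspected risk, and on the therapist being the one who calls. The size cannot be stated from the document. The effect is on the deviation report and on consistent conduct, not on the primary estimate, alpha or sample size. It should be corrected because the text is wrong as it stands and the correction is cheap.

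**What to change.** Reconcile The role of the therapist, {11b} and {22} on two questions: whether the risk assessment is optional or required, and whether a telephone call made for it counts as a deviation. The clinical rule is for the sponsor to decide; none is proposed here. State also that the scheduled inactivity call in {11c} lies outside the deviation label.

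In the eCRF, give calls that the protocol prescribes a reason code separate from unplanned telephone contact, and report both by arm.

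The cost is a wording amendment and one eCRF field. Inclusion is expected to run to August 2026 (Trial status), so a change made before then would apply to later participants. Earlier calls can be recoded only where a reason was recorded; the article says calls are logged, but not that the reason is.

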### Criteria for discontinuing or modifying allocated interventions {11b}

Participants may withdraw their consent to participate in the treatment and the trial at any timepoint. Suicidal ideation triggers a structured suicide-risk assessment (e.g., C-SSRS plus focused interview on intent, plan, means, and protective factors) and, if indicated, referral. All safety assessments are conducted remotely (telephone or secure video), no face-to-face visits are planned. The intervention may be temporarily titrated or discontinued for (a) acute suicide risk requiring urgent care or (b) emergent medical/psychiatric conditions that render participation unsafe. Acute risk is managed per the study safety protocol with immediate escalation and referral to regular care (e.g., emergency psychiatric services, local outpatient psychiatry, emergency department). Participants who discontinue the intervention are invited to continue all scheduled outcome assessments when clinically appropriate.

### Strategies to improve adherence to interventions {11c}

The platform sends automated SMS reminders at each scheduled weekly monitoring point and an SMS notification whenever a therapist posts a message. If a participant has not logged in for 3 consecutive days, the therapist sends a personalized SMS via the platform to prompt engagement. If inactivity reaches 5 consecutive days, the therapist attempts telephone contact; if phone contact cannot be established, a letter is mailed within the same week. Automated digital reminders continue, and the therapist re-attempts contact weekly thereafter unless the participant withdraws consent. (This escalation schedule is identical across trial arms.)

Participants who discontinue treatment are retained in follow-up whenever possible and invited to complete all scheduled outcome assessments; this approach minimizes attrition bias and supports valid intention-to-treat analyses.

The therapist delivering the treatments in the trial will comprise resident psychologists (a 1-year post-degree licensure period following a 5-year MSc in Psychology). All clinicians are based at a specialized PTSD unit and deliver treatment in both trial arms. All therapists will receive training in and a written treatment manual for both treatment arms. Supervision by certified supervisors and trainers in prolonged exposure and/or CBT will be offered weekly.

Blinded assessors will undergo a minimum of a full-day training in the CAPS-5 prior to conducting clinician-rated assessment with CAPS-5 and practice by rating videos of fictious PTSD case examples. Assessors who deviate more than 10% of the CAPS-5 total score agreed upon by one of the authors (MB) and score more than one point differently on a maximum of four single items will need to retake the training. The assessors are offered weekly supervision.

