### Outcomes {12}

The primary outcome measure is the CAPS-5, the gold-standard clinical interview that evaluates the severity of PTSD symptoms and determines the presence of PTSD in the past month [12]. This evaluation will be conducted at multiple time points: upon enrollment, 1 month after completing the treatment (primary endpoint), and during the 6- and 12-month follow-up assessments. The CAPS-5 total severity score has been shown to exhibit strong internal consistency (Cronbach’s *α* = 0.88) and interrater reliability (intraclass correlation coefficient = 0.91), along with favorable test–retest reliability (intraclass correlation coefficient = 0.78) [12]. Treatment response will be considered achieved if there is a minimum of 10 points improvement on the CAPS-5 between baseline and the participant’s last available measurement within the baseline to 12-month follow-up period (adapted from [13]). Remission will be defined as the absence of a PTSD diagnosis or a CAPS-5 total symptom severity score below 12 [13]. To be classified as having achieved recovery, participants must maintain their remission status at both the 6-month and 12-month follow-ups.

Secondary self-rated outcome measures include the Posttraumatic Stress Disorder Checklist for DSM-5 (PCL-5) [14] and the International Trauma Questionnaire (ITQ) [15] to capture self-rated symptoms of PTSD and complex PTSD. The Patient Health Questionnaire (PHQ-9; [16]) and the EuroQol 5-dimensions (EQ-5D; [17]) will be used to assess the level of depressive symptoms and quality of life. Treatment response on the PCL-5 will be defined as a drop of 10 points or more. For remission, a score below 30 will be used, which has been identified as indicative of probable PTSD in the Swedish version of the PCL-5 [18].

To calculate quality-adjusted life-years for cost-utility analysis, participants will complete the Assessing Quality of Life 6 Dimensions (AQoL-6D; [19]). Data concerning the utilization of medical resources, medication, social care, absenteeism, and presenteeism in relation to employment will be collected using The Treatment Inventory of Costs in Patients with psychiatric disorders (TIC-P; [20]). Moreover, information on adverse events will be gathered using the Negative Effects Questionnaire (NEQ) immediately after treatment completion and the upcoming assessment points [21]. Participants will also receive an open-ended question asking for the occurrence of adverse events weekly during treatment.

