### Sample size {14}

A priori power analysis determined the sample size for comparing HOPE with an active control at the primary endpoint (1 month). Based on prior internet-delivered CBT work showing a between-group effect of Cohen’s *d* = 0.38 [8], we powered the trial to detect a conservative effect of *d* = 0.35 with 80% power at a two-sided *α* = 0.05 under 1:1 randomization. This yields *n* = 129 per group at the primary endpoint. To accommodate 10% data attrition (missing primary outcome), consistent with retention in other therapist-guided digital trials [11], we inflated the sample to *N* = 286 (143 per arm), expected to retain 129 per arm for analysis.

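### As worded, the CAPS-5 assessor retraining rule spares an assessor who misrates five or more items, and one whose errors cancel in the total

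*Protocol article*

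**What the plan says.** The rule stands in the Protocol article, Strategies to improve adherence to interventions {11c}. Its setting is training before any trial rating is made: "Blinded assessors will undergo a minimum of a full-day training in the CAPS-5 prior to conducting clinician-rated assessment with CAPS-5". Trainees practise on videos of invented cases, and their ratings are compared with a score set by one of the authors.

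The threshold is one sentence with two conditions joined by *and*. The first concerns the total: "Assessors who deviate more than 10% of the CAPS-5 total score agreed upon by one of the authors". The second concerns single items: they "score more than one point differently on a maximum of four single items will need to retake the training".

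No other section gives a different certification threshold. The one continuing safeguard in the same section is optional in its wording: "The assessors are offered weekly supervision". The Outcomes {12} section states what these assessors measure: "The primary outcome measure is the CAPS-5, the gold-standard clinical interview". It also defines remission as either no PTSD diagnosis or a CAPS-5 total below 12.

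**The concern.** The sentence has two separate faults.

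- **Direction of the item limit.** A cap of four describes acceptable performance. Placed inside the failing condition, it makes that condition false as soon as a fifth item is badly scored. The worse rater then escapes where the better one is caught.
- **The connector.** With *and*, agreement on the total is enough to avoid retraining, however many items are wrong, provided the errors balance.

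This is the only stated pass/fail threshold for the people who rate the primary outcome. CAPS-5 is also used to decide eligibility (Participant timeline {13}) and enters the remission definition, where absence of a diagnosis counts separately from the total. If diagnosis rests on particular symptoms, item errors that cancel in the total could still change it. Under Who will be blinded {17a}, a participant who discloses the allocation is moved to another assessor at later follow-ups. Disagreement between assessors can then enter that participant's change score.

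**Working it through.** **The plan's own figure, for orientation.** The Sample size {14} section plans for d = 0.35 "with 80% power at a two-sided" alpha of 0.05. The two-sample calculation returns 129 per arm, as stated. With 10% attrition, 143 × 0.9 = 128.7, in line with the stated retention. None of these quantities enters the retraining rule.

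**Inputs from the document.** Total limit: 10% of the agreed score. Item limit: a difference of more than one point, on at most four items. Connector: *and*.

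**Assumption not in the document.** 20 items scored 0 to 4, with an agreed score of 2 on every item, so an agreed total of 40.

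**Formulas.** D = |assessor total − agreed total| / agreed total. K = number of items off by more than one point.

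- Literal rule: retrain if D > 10% and K ≤ 4.
- Only the item limit turned round: retrain if D > 10% and K > 4.
- Both corrected: retrain if D > 10% or K > 4.

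| Constructed assessor | D | K | Literal | Only limit turned | Both corrected |
|---|---|---|---|---|---|
| 3 items at +2 | 6/40 = 15% | 3 | retrain | no | retrain |
| 4 items at +2 | 8/40 = 20% | 4 | retrain | no | retrain |
| 5 items at +2 | 10/40 = 25% | 5 | no | retrain | retrain |
| 20 items at +2 | 40/40 = 100% | 20 | no | retrain | retrain |
| 5 items at +2, 5 at −2 | 0/40 = 0% | 10 | no | no | retrain |
| 10 items at +1 | 10/40 = 25% | 0 | retrain | no | retrain |

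The literal column reverses between four and five items: 20% off leads to retraining, and 25% or even 100% off does not. This reversal does not depend on the assumed scale, because K ≤ 4 alone decides it. The cancelling case likewise needs only a net deviation of zero.

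The fifth column shows that turning the item limit round is not enough. With *and* kept, the cancelling assessor still passes, and so do the assessors 15% and 20% off in total. Both the direction and the connector have to change.

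**The case against.** The strongest reply is that the intention can be recovered: pass if the total is within 10% and no more than four items are off by more than one point. A trainer is unlikely to retrain someone with three bad items and clear someone with twenty. Assessors also receive at least a day of training, practise against an agreed score and have supervision on offer, and inclusion is decided jointly with the principal investigator. This stands as far as it goes. It makes a drafting error the likely explanation, but it does not tell the reader which rule was applied or whether a joint trigger was meant.

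A reader might infer three stronger things, which the article does not support:

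- **That poorly calibrated assessors have been rating the primary outcome.** The article reports no certification results. That such assessors would pass is inferred from the absence of any other threshold.
- **That the trial loses power.** Nothing in the article links this sentence to any amount of added variance. The planned d = 0.35 was set just below an effect observed in an earlier trial, and an observed standardised effect already contains ordinary rating error. Assessors are masked, so poor calibration would be expected to add noise and not to favour an arm.
- **That an assessor far off through many one-point errors also escapes.** On the literal reading this is false: no item is off by more than one point, zero is within a maximum of four, and a total 25% off then triggers retraining.

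**Conclusion.** Wrong as written. Followed literally, the rule exempts any assessor with five or more items off by more than one point, and any assessor whose errors cancel in the total. It catches one with three or four such items once the total is off by more than 10%. The five-item result needs no assumption about the scale; the percentages in the table assume 20 items and an agreed total of 40. The fault is in a decision threshold that guards the quality of the primary outcome, and it is most likely one of drafting. There is no evidence that it changed who was certified, and the sample size, power and alpha stand unchanged.

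**What to change.** Restate the sentence as a pass criterion. For example: an assessor is cleared when the CAPS-5 total lies within 10% of the agreed score and no more than four items differ from it by more than one point; exceeding either limit means the training is repeated.

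Then state which version has been applied since inclusion began in September 2023. If it was the intended pass criterion, the correction ends there. If it was the literal sentence, re-check the training ratings of assessors already cleared. Inclusion is expected to run to August 2026 and follow-up to October 2027, so later ratings can still be protected.

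The cost is one sentence, a short statement of practice and possibly a review of existing training ratings. The downside is small: a few assessors may have to repeat the one-day training.
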